#### During Completion of Questionnaires:

Questionnaires of anxiety and mood will be completed at pre-education, prior to completing each new lesson, at post-education, at 3 month follow-up, and for Groups 2, 3, and 4, also at again at 12 month follow-up.

Any deterioration in mood or elevated distress will trigger protocols involving contacting the participant to discuss their emotional state, and a meeting between the Clinical Psychologist and Chief Investigator/other researchers to develop a management plan, which is then documented and followed up as per VirtualClinic policy.

Members of the research team will meet at least 2 X weekly to discuss progress of each participant and of the overall trial. The Chief Investigator will monitor overall progress weekly and will take overall responsibility for this trial. All communications with participants will be documented as per VirtualClinic documentation policies. All adverse events will be promptly reported to the HRECs and CRUfAD Director.

#### 5.4. RECRUITMENT AND SCREENING

##### Recruitment

Recruitment involves the following steps:

1. The study will be described on the intake website, [www.virtualclinic.org.au](http://www.virtualclinic.org.au). People will read the information about the study and elect to continue or not. If they choose to apply for the study they will complete an automated screening questionnaire to screen out participants with a history of schizophrenia or bipolar disorder, active suicidality, severe symptoms of depression, current substance use/dependence, or those who are asymptomatic.
2. People whose responses to the questions meet selection criteria will be telephoned by the researchers at a time convenient to the participant to administer a diagnostic interview (the Mini International Neuropsychiatric Interview Version 5.0.0 (MINI)) [23] to determine whether the participant meets criteria for an anxiety disorder. Note that meeting diagnostic criteria for a formal anxiety disorder or depression is NOT an inclusion criterion – instead, participants need to have elevated symptoms of anxiety as measured by outcome questionnaires.
3. Applicants assessed at diagnostic telephone interview as having a primary diagnosis of post-traumatic stress disorder, obsessive compulsive disorder or another disorder not targeted by this education protocol will not be eligible for this program, but will be informed about other more appropriate iCBT programs as well as being encouraged to consider other education and treatment options including accessing their GP or local services.
4. Those who meet the inclusion criteria will be randomly allocated to one of the four groups.
5. Participants will be sent the Participant Information Sheet and Consent Form via email and will return an electronic consent form via email to the investigators.

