## 5.STUDY OUTLINE

### 5.1. STUDY FLOW TABLE

| Date         | Stage                                                                                                               | Groups                                                                              |                                                                                                                             |                                                                                                                             |                                                                                                                             |
|---------------------|----------------------------------------------------------------------------------------------------------------------------|--------------------------------------------------------------------------------------------|-----------------------------------------------------------------------------------------------------------------------------|-----------------------------------------------------------------------------------------------------------------------------|-----------------------------------------------------------------------------------------------------------------------------|
| February-March 2011 | Recruitment                                                                                                                | Eligible applicants randomized to:                                                         |                                                                                                                             |                                                                                                                             |                                                                                                                             |

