  - b. Learn about the principles of CBT
2. *Lesson 2:*
  - a. Learn about the relationship between the way you think and feel
  - b. Begin monitoring and challenging unhelpful thinking patterns
3. *Lesson 3:*
  - a. Learn about physical symptoms of anxiety and depression and managing these with de-arousal and activation techniques
  - b. Assertiveness skills
4. *Lesson 4:*
  - a. Learn about behaviours (low activity and avoidance) that make anxiety and depression worse, and how to challenge those behaviours
5. *Lesson 5:*
  - a) Learn about problem solving, relapse prevention and staying well

On application, applicants will complete screening measures of anxiety and depression. Those with scores too high or too low (asymptomatic) will not be eligible. Eligible applicants will be telephoned by

the researchers, who will conduct diagnostic interviews via telephone. Applicants who meet diagnostic criteria for a primary disorder other than those targeted by this education protocol will not be eligible but will be informed about other options for education or treatment.

At the beginning of the education program all participants will complete the outcome measure questionnaires. The questionnaires being administered in this study are all valid and reliable clinical and research measures.

All participants will complete a second entire set of questionnaires at the post-education point (Primary Endpoint) and will also be telephoned by the researchers who will conduct the telephone interviews again. Participants in Groups 2, 3 and 4 will also be asked to complete a shorter set of questionnaires at 3 and 12 months follow-up. Participants in Group 1 (Waitlist control group) will begin the program immediately after the other groups have completed the education.

In addition, brief measures of anxiety and depression (the GAD-7 and PHQ-9) will be administered at the beginning of each lesson to monitor anxiety and mood. We will also encourage feedback from participants at every stage of the project to determine how to improve the content and delivery of the program.

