#### 5.5. INFORMED CONSENT PROCESS

Only participants who have read the information about the studies, elected to complete the screening questionnaire and meet inclusion criteria, will be invited to participate. A Participant Information Form and Consent Form will then be emailed to the participant. Informed consent will be taken as successfully returning the Consent Form. Additionally, informed consent will also be monitored during the study by the Chief Investigator; each time a patient logs on to do a lesson will be taken as a sign of continued consent to participate.

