#### 5.6. ENROLMENT PROCEDURE

Once participants have been accepted into the study they will receive an email confirming that they have been accepted pending return of their Consent Form. Once they have returned their Consent Form they will receive another email confirming this receipt and confirming the start date of the program.

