#### 5.7. RANDOMIZATION PROCEDURE

The website [www.random.org](http://www.random.org) will be used to determine a list of randomly generated numbers that correspond to a group. Such a list will be generated by an overseas colleague. Participants will be randomly allocated to one of the four groups after they complete the diagnostic interview.

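### Random allocation is placed before consent and before the baseline questionnaires, and the sections disagree on when the eligibility interview takes place

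*Protocol*

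**What the plan says.** Section 5.4 (Recruitment) presents recruitment as a numbered sequence. Step 2 is the telephone diagnostic interview and step 3 turns away people with a non-target primary diagnosis. Step 4 reads "Those who meet the inclusion criteria will be randomly allocated to one of the four groups", and step 5 reads "Participants will be sent the Participant Information Sheet and Consent Form via email and will return an electronic consent form".

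Section 5.5 says that people who meet the criteria are invited and that "A Participant Information Form and Consent Form will then be emailed to the participant". It does not say whether this happens before or after allocation. Under Section 5.6, accepted people first learn that "they will receive an email confirming that they have been accepted pending return of their Consent Form". After the form is back, "they will receive another email confirming this receipt and confirming the start date of the program".

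On the baseline, Section 5.2 states: "At the beginning of the education program all participants will complete the outcome measure questionnaires". The flow table in Section 5.1 has the entry "Eligible applicants randomized to" in its February-March 2011 recruitment row, above the four group columns. The pre-education questionnaires and a diagnostic interview appear in the April 2011 row below it.

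On the interview, Section 5.7 says "Participants will be randomly allocated to one of the four groups after they complete the diagnostic interview". Section 7 states that the trial is not blinded, and Section 8.2 promises intention-to-treat and completer analyses, with ANCOVAs and mixed linear models among the methods.

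**The concern.** Randomisation protects a comparison from the moment of allocation, provided that everyone allocated is kept and that what is called baseline was fixed beforehand. The stated order weakens both conditions.

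First, Section 5.5 treats return of the form as consent. A person allocated at step 4 who does not return it at step 5 has a group but no usable data. The intention-to-treat set then becomes the people who were allocated and later consented, which is a selection made after randomisation.

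Secondly, Groups 2 to 4 start at once and Group 1 starts at week 9, so a start date tells a person whether they are on the waitlist. If that date arrives before the pre-education questionnaires, self-reported baseline scores may reflect the news. Adjusting for such a score, or measuring change from it, brings an effect of allocation into the comparison.

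Thirdly, the interview decides whether a person is excluded for a non-target primary disorder. It should have one unambiguous place, before allocation.

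**Working it through.** The plan gives no figure on this point to reproduce. The main check is to set the statements side by side.

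| Event | Where stated | Position relative to allocation |
|---|---|---|
| Online screen, including PHQ-9 and GAD-7 cut-offs | 4.1; 5.2; 5.4 step 1 | Before |
| Diagnostic interview | 5.4 steps 2-4; 5.7 | Before |
| Diagnostic interview | 5.1, April row | After |
| Information sheet and consent form | 5.4 step 5 | After |
| Information sheet and consent form | 5.5; 5.6 | Not stated |
| Start-date email | 5.6 | After consent is returned |
| Pre-education outcome questionnaires | 5.1, April row; 5.2 | After |

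**Consent.** Only Section 5.4 fixes its place relative to allocation, and it fixes it afterwards. No section reverses this.

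**Baseline.** Sections 5.1 and 5.2 agree that it follows allocation. The start-date email goes out when the form is received, and the questionnaires are completed when the program begins, so the email can come first.

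**Scores that exist before allocation.** PHQ-9 and GAD-7 are screening measures (Section 4.1), so each has a pre-allocation value. None is described for DASS-21, PDSS-SR, SP-12, WHODAS-II, K-10 or the NEO-FFI neuroticism scale.

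**Interview.** Sections 5.4 and 5.7 contradict the row order of the flow table.

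The following illustrations of size rest on assumed inputs, because the documents give none. The yardstick is the planned Group 1 difference of 0.55 (Section 8.1).

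*A. Loss between allocation and consent.* Suppose a share p of Group 1 is lost and the lost people differ by m SD from the mean of the whole allocated arm. The mean of those who remain moves by p × m / (1 − p).
- p = 0.05, m = 0.25: 0.05 × 0.25 / 0.95 = 0.013 SD.
- p = 0.10, m = 0.5: 0.10 × 0.5 / 0.90 = 0.056 SD.
- p = 0.20, m = 0.5: 0.20 × 0.5 / 0.80 = 0.125 SD.

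The direction is unknown. If the more severe cases leave, the remaining waitlist looks better and the contrast shrinks. If the milder cases leave, it grows.

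*B. Baseline shifted by knowledge of the wait.* Suppose Group 1 baseline scores rise by δ and the ANCOVA slope is b. The adjusted contrast moves by b × δ.
- b = 0.3, δ = 0.1: 0.03 SD.
- b = 0.5, δ = 0.2: 0.10 SD.
- b = 0.7, δ = 0.2: 0.14 SD.

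A raised Group 1 baseline lowers that group's adjusted outcome score, so this shift shrinks the benefit over waitlist and works against the hypothesis. A lowered baseline would do the reverse.

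A and B may oppose each other, so their sizes must not be summed.

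*C. Power, if loss is equal across arms.* For 0.55 with 50 versus 100, two-sided 0.05, power is Φ(0.55 / √(1/n₁ + 1/n₂) − 1.96). With no loss this is Φ(3.175 − 1.96) = 0.89. With 5%, 10% and 20% lost from each arm it is 0.87, 0.85 and 0.81. Loss of power is therefore minor; what matters is who is lost.

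**The case against.** A reader might infer that people decide on consent already knowing their group. The documents do not show this. Section 5.6 sends the start date only after the form is returned, and no section discloses the group sooner. The word for confirming a date could hint at earlier notice, but nothing else supports that. Inclusion criterion 9 also requires people to be prepared to consent, which narrows later refusal without removing it. What stands is that consent follows allocation and that no statement keeps the group undisclosed until the form is back.

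A reader might also infer that exclusions are made by researchers who know the arm. That could happen only if the flow-table order were followed. Sections 5.4 and 5.7 say otherwise, and the table itself refers to applicants who are already eligible. Its April row may simply list the contents of the pre-education assessment. This part is a contradiction to reconcile, not evidence of biased exclusion.

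Thirdly, Section 8.2 names no ANCOVA covariate, so use of the April score is an assumption. For PHQ-9 and GAD-7 the screening score could serve instead. The choice of covariate is properly left to a statistical analysis plan, and its absence here is not a fault. The order of consent, baseline and allocation, however, belongs in the protocol, and no analysis can recover people lost between allocation and consent.

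Finally, Groups 2, 3 and 4 share a start date. The start-date email therefore cannot disturb the 0.35 comparisons among them.

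**Conclusion.** The point holds in this form. Followed as written, an unblinded trial with self-report outcomes allocates people before they consent and collects its outcome baseline after allocation. The intention-to-treat set is then open to selection after randomisation, and the pre-education scores can be affected by knowing whether one has to wait. The second mechanism concerns the contrast of Group 1 with Groups 2 to 4. It matters most for the six outcome scales that have no screening score.

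Bias is possible, not demonstrated. Under the assumed inputs, loss before consent moves the waitlist contrast by 0.01 to 0.13 SD in either direction. A baseline raised in Group 1 shrinks it by 0.03 to 0.14 SD. At most that is about a quarter of the planned 0.55 (0.14 / 0.55 = 0.25). These ranges depend entirely on the assumed loss, difference, shift and slope.

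The position of the diagnostic interview is a separate inconsistency, and Sections 5.1, 5.4 and 5.7 must be reconciled on it.

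**What to change.** State one order, in the same terms, in Sections 5.1, 5.2 and 5.4 to 5.7:

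1. online screen;
2. consent form returned;
3. diagnostic interview and final eligibility decision;
4. pre-education questionnaires completed;
5. random allocation;
6. group and start date disclosed.

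The independent colleague who generates the list could release each assignment only once steps 1 to 4 are logged. Section 5.2 needs amending as well, because it ties the questionnaires to the start of the program. Define intention-to-treat as everyone allocated under this order.

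The change resequences existing online and telephone steps and adds no visits or assessments. It has two costs. Applicants who do not finish the baseline are lost before randomisation instead of after it, which reduces the number available but protects the comparison. And because recruitment runs in February-March with an April start, either the baseline is some weeks old for early recruits or allocation is held until shortly before April. The protocol should say which of these it accepts.

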#### 5.5. INFORMED CONSENT PROCESS

Only participants who have read the information about the studies, elected to complete the screening questionnaire and meet inclusion criteria, will be invited to participate. A Participant Information Form and Consent Form will then be emailed to the participant. Informed consent will be taken as successfully returning the Consent Form. Additionally, informed consent will also be monitored during the study by the Chief Investigator; each time a patient logs on to do a lesson will be taken as a sign of continued consent to participate.

#### 5.6. ENROLMENT PROCEDURE

Once participants have been accepted into the study they will receive an email confirming that they have been accepted pending return of their Consent Form. Once they have returned their Consent Form they will receive another email confirming this receipt and confirming the start date of the program.

#### 5.7. RANDOMIZATION PROCEDURE

The website [www.random.org](http://www.random.org) will be used to determine a list of randomly generated numbers that correspond to a group. Such a list will be generated by an overseas colleague. Participants will be randomly allocated to one of the four groups after they complete the diagnostic interview.

### 6. SAFETY

#### 6.1. ADVERSE EVENT REPORTING

Regular team meetings (at least 2 times a week) will be conducted to monitor any difficulties participants may be having and ways of best dealing with these difficulties. Adverse events will be reported to the Ethics Committee.

#### 6.2. SERIOUS ADVERSE EVENT REPORTING

Serious adverse events will be reported to the HRECs via SAE documentation and emails. Such information will also be reported to the CRUfAD Director, [name], and discussed at additional meetings of the researchers. All researchers work at the same site (St Vincent's Hospital), facilitating the ability to hold urgent or unplanned meetings.

#### 6.3. PARTICIPANT SAFETY

During the trial all participants will be screened before completing each lesson when they complete brief measures of anxiety and depression. All electronic communications (emails) contain contact details for emergency services (in the footer), and written details about staying safe in mental health emergencies are included in several locations in the program materials.

Questionnaires of anxiety and mood will be completed at pre-education, before each of the 5 lessons, and at 3-month and 12-month follow-up. Any deterioration in mood or elevated distress triggers protocols involving contacting the participant to discuss their emotional state, and a meeting between the Clinical Psychologist and Chief Investigator/Other researchers to develop a management plan, which is then documented and followed up as per VirtualClinic policy. Participant safety and wellbeing is the paramount consideration. Participants will be invited to contact the investigators at any time should their wellbeing deteriorate.

#### 6.4. DATA SAFETY AND MONITORING BOARD

Data safety will comply with the National Statement on Ethical Conduct in Human Research [24]. Only the responsible clinicians, delegated research assistants, and Chief Investigator will see identified data. To maintain participant privacy and confidentiality, participants will not be able to use an alias/username that contains identifiable information (e.g real name). If they choose an alias/username that contains identifiable information, they will be requested to change it before beginning the Program.

#### **6.5. EARLY TERMINATION**

If a patient wishes to withdraw from the study once it has started, he or she can do so at any time without having to give a reason. This process will be supervised by the Chief Investigator. Upon early withdrawal, all participants will be provided with encouragement to access additional services via their GP. Additionally, all participants will be given the opportunity to provide feedback about their current symptoms. If participants withdrawing from the program do report a deterioration of their symptoms, they will be contacted by the Clinical Psychologist or Chief Investigator to discuss access to additional services. If participants do not choose to provide feedback about their symptoms, but the investigators have concerns about the participant's condition, we do have consent from all participants to contact their GP. This process will be supervised by the Chief Investigator.

### **7. BLINDING AND UNBLINDING**

Study is not blinded.

### **8. STATISTICAL CONSIDERATIONS**

#### **8.1. SAMPLE SIZE CALCULATION**

The design is powered to detect a between-groups effect size difference of 0.35 (alpha of 0.05, and power of 0.80) between Groups 2, 3, and 4, requiring 100 participants in Groups 2, 3, and 4. The design is also powered to detect a between-groups effect size difference of 0.55 between Group 1 and Groups 2, 3, and 4, requiring 50 participants in Group 1.

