| Study procedure:       | Recruit and treat participants with elevated symptoms of depression and/or anxiety using a 5-lesson Internet-based education program. Three groups begin the program immediately, with graded levels of support (none vs. automatic emails vs. automatic emails + weekly phone calls). Their results are compared with a waitlist control condition.                                                                                                                                                                                                                  |
| Stat considerations:   | The design is powered to detect a between-groups effect size difference of 0.35 (alpha of 0.05, and power of 0.80) between Groups 2, 3, and 4. The design is also powered to detect a between-groups effect size difference of 0.55 between Group 1 and Groups 2, 3, and 4. Analyses will be conducted using intention-to-treat and completer models. Categorical data will be analysed via chi-squared tests and continuous data via parametric or equivalent non-parametric tests, including ANCOVAs and mixed linear models.                                       |
| Duration of the Study: | 23 months                                                                                                                                                                                                                                                                                                                                                                                                                                                                                                                                                             |

| TABLE OF CONTENTS                                                      | PAGE |
|------------------------------------------------------------------------|------|
| 1. BACKGROUND                                                          | 5    |
| 1.1 Disease Background                                                 | 5    |
| 1.2 Rationale for Performing the Study                                 | 5    |
| 2. STUDY OBJECTIVES                                                    |      |
| 2.1 Primary Objective                                                  | 6    |
| 2.2 Secondary Objective                                                | 7    |
| 3. STUDY DESIGN                                                        |      |

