## **2. STUDY OBJECTIVES**

### **2.1. PRIMARY OBJECTIVES AND HYPOTHESES AND ENDPOINTS**

To determine the benefits of different levels of support on the efficacy of an internet-delivered trans-diagnostic iCBT education program for anxiety and depression, using a 4-group CONSORT-R compliant, registered RCT.

The main hypotheses are that

1. Improvements will be observed at Primary Endpoint (post-education) in symptoms of anxiety and depression: Groups 4>3>2>1
2. Differences will be observed in the acceptability of the program: Groups 3>2>1
3. Differences will be observed in completion rates: Groups 3>2>1

The Primary Endpoint coincides with the post education questionnaires at week 9.

The Secondary Endpoint occurs at 3-month follow-up.

The Tertiary Endpoint occurs at 12-month follow-up.

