#### **8.2. ANALYSIS PLAN**

Analyses will be conducted using intention-to-treat and completer models. Categorical data will be analysed via chi-squared tests, and continuous data via parametric or equivalent non-parametric tests including ANCOVAs and mixed linear models.

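### Section 8.1 claims 80% power for 0.35 between Groups 2, 3 and 4, but 100 per group gives about 69% on the usual two-sided unadjusted test; 80% needs conditions the protocol does not state

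*Protocol*

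**What the plan says.** Section 8.1 makes two power statements. For the three active groups, it describes the trial as "powered to detect a between-groups effect size difference of 0.35 (alpha of 0.05, and power of 0.80) between Groups 2, 3, and 4". It sets the size of each of these groups at 100. For the waitlist comparison it gives an "effect size difference of 0.55 between Group 1 and Groups 2, 3, and 4, requiring 50 participants in Group 1". The Summary repeats both effect sizes and the same alpha and power.

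Neither place states sidedness, the test, a baseline correlation or an allowance for missing outcomes. Two other places bear on how the figures might have been obtained. Section 2.1 words the main hypothesis directionally, for "symptoms of anxiety and depression: Groups 4>3>2>1". Section 8.2 lists "parametric or equivalent non-parametric tests including ANCOVAs and mixed linear models" for continuous data, without linking any of them to the sample size.

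**The concern.** Comparing levels of support is the primary objective, so the power statement for Groups 2, 3 and 4 is the one on which the trial's main question depends. An alpha of 0.05 with no qualifier is ordinarily read as two-sided, and on that reading 100 per group falls well short of 80% power for a difference of 0.35.

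If the 80% is taken at face value, a non-significant difference between support levels could be given more weight as evidence of no benefit than the design supports. On the two-sided unadjusted reading, the chance of missing a true difference of 0.35 is 1 − 0.692, about 31%, with complete data, rather than 20%.

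**Working it through.** **Inputs from Section 8.1.** Effect sizes d = 0.35 and d = 0.55 (SD taken as 1), alpha 0.05, power 0.80, 100 in each of Groups 2, 3 and 4, and 50 in Group 1. The power of 0.80 is attached to the 0.35 statement; it is assumed here for 0.55 when a sample size is solved for.

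**Formulas.** For equal groups, n per group = 2(z_alpha + z_power)² / d². For groups of n1 and n2, power ≈ Φ(d·√[n1·n2/(n1+n2)] − z_alpha). Here z_power = 0.842, and z_alpha = 1.960 two-sided or 1.645 one-sided. Noncentral t results follow each normal approximation and are the figures used in the conclusion.

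**Reproducing the 100 (d = 0.35, 100 v 100).** The standardised signal is 0.35 × √50 = 2.475.

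| Reading | n per group for 80% | Power at 100 per group |
|---|---|---|
| One-sided, unadjusted | 2(2.487)²/0.1225 = 100.9, so 101; t: 102 | Φ(2.475 − 1.645) = 0.797; t: 0.794 |
| Two-sided, unadjusted | 2(2.802)²/0.1225 ≈ 128.1, so 129; t: 130 | Φ(2.475 − 1.960) = 0.697; t: 0.692 |

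The stated 100 therefore reproduces one-sided and not two-sided. The difference detectable with 80% power, two-sided, is 2.802 × √(2/100) = 0.396; t: 0.398, or about 0.40.

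**Baseline-adjusted route.** ANCOVA replaces d by d/√(1 − r²), where r is the pre-post correlation. The protocol gives no r, so these values are assumptions. Power is two-sided, 100 v 100, complete data:

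| Assumed r | Adjusted d | Power |
|---|---|---|
| 0.40 | 0.382 | 0.77 |
| 0.48 | 0.399 | 0.80 |
| 0.50 | 0.404 | 0.81 |
| 0.60 | 0.4375 | 0.87 |

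So r of about 0.48 also gives the stated figure.

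**An overall three-group test.** With the extreme groups 0.35 apart and the middle group midway, power at 100 per group is 0.59. With two groups equal and the third 0.35 away, it is 0.72. Neither gives 0.80.

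**Checking the convention against the 50 (d = 0.55).**

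- Two-sided, equal arms: 2(2.802)²/0.3025 = 51.9, so 52; t: 53. Power at 50 v 50 is Φ(2.75 − 1.960) = 0.785; t: 0.777. This is close to the stated 50.
- One-sided, equal arms: 2(2.487)²/0.3025 = 40.9, so 41; t: 42. This does not give 50.
- Two-sided ANCOVA with r of about 0.48, equal arms: about 41. This does not give 50 either.
- Actual allocation, 50 v 100, two-sided: 0.55 × √(5000/150) = 3.175, and Φ(3.175 − 1.960) = 0.888; t: 0.884. The 0.55 claim is met.

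The two routes that give 100 do not give 50, and the route that gives about 50 does not give 100.

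**Missing outcomes.** The protocol gives no rate, so a range is assumed. Power for d = 0.35, with each missing outcome counted as a lost participant:

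| Assumed missing | Two-sided, unadjusted | One-sided, unadjusted | Two-sided ANCOVA, r = 0.5 |
|---|---|---|---|
| 0% | 0.69 | 0.79 | 0.81 |
| 10% | 0.65 | 0.76 | 0.77 |
| 20% | 0.59 | 0.71 | 0.72 |
| 30% | 0.54 | 0.66 | 0.66 |

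**The case against.** The best defence is that a two-sided unadjusted test is the reader's assumption and not the protocol's. The main hypothesis is directional, and a one-sided 5% test gives 79% power. ANCOVA is among the planned methods, and a moderate baseline correlation gives 80% two-sided. Either route reaches 100 per group with one unstated input. This defence stands against the stronger reading a reader might infer, that the 80% is simply wrong: the documents show a calculation that is under-specified, not one that is impossible to obtain.

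It does not clear the paragraph. A directional expectation is not a specification of a one-sided test, and no such test appears in Section 8.2. Neither route gives the 50 required in the next sentence.

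A reader might also infer that the 0.55 statement is an error in the other direction. It is not. The design is powered for 0.55 at the actual allocation, and 50 is at most conservative. Its relevance is only that it points to a different convention.

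Nor should the lack of a multiplicity adjustment across the pairwise comparisons be held against Section 8.1, because that may be settled in a statistical analysis plan.

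Finally, the missing-data figures are somewhat pessimistic if a mixed model uses the PHQ-9 and GAD-7 scores collected before each lesson, since a participant without a week-9 score may still contribute. The protocol does not rest its power on that.

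**Conclusion.** The point holds in conditional form. If Groups 2, 3 and 4 are compared two-sided at 5% without baseline adjustment, 100 per group gives about 69% power for 0.35; 80% needs 130 per group or a true difference of 0.40. The stated 80% needs either a one-sided test (0.79) or a two-sided ANCOVA with a correlation of about 0.48 (0.80). The protocol states neither condition, and with complete outcomes there is no margin: an assumed 10% loss takes the one-sided figure to 0.76.

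The inconsistency between the 100 and the 50 does not depend on which sidedness one prefers, since no single convention tried gives both. The arithmetic is certain; what the authors intended is not. The correlations and missing-data rates are assumptions.

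**What to change.** Revise Section 8.1 and the matching Summary entry in one of two ways.

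1. State that tests are two-sided, and give the unadjusted figures before dropout: 100 per group has 69% power for 0.35 and 80% power for 0.40; 50 against 100 has 88% power for 0.55.
2. Base both calculations on the baseline-adjusted ANCOVA already named in Section 8.2, and state the assumed pre-post correlation with its justification. A correlation of about 0.5 gives 81% for 0.35 with complete data, or 72% with an assumed 20% missing.

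Under either option, add the figures after the expected dropout. The cost is a change of wording in two places, with no extra participants. The drawback is a less favourable stated power under option 1, or under option 2 once dropout is counted.
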